### Evaluation Objectives and Research Questions

#### Objective 1

The first objective is to evaluate the impact of the Medly Program on health service utilization, patient health outcomes, and their ability to self-care. Alerts sent to patients and clinicians will help identify periods of symptom exacerbation and volume overload. The impact of this is expected to permit earlier intervention for worsening conditions, thus avoiding trips to the emergency department (ED) and hospitalizations. For patients who are enrolled into the Medly Program on hospital discharge, the program is expected to reduce 30-day readmission rates. In addition, participation in the Medly Program is expected to improve patients’ ability to self-care, leading to improved clinical outcomes and QoL.

#### Objective 2

The second objective is to evaluate the degree to which the Medly Program was implemented as intended and to identify the contextual barriers and facilitators of implementation. This objective will answer the following questions:

To what extent did the HF clinic implement the Medly Program as intended?What contextual factors influence the implementation of the Medly Program?What adaptations were needed to implement and sustain the program within existing clinical workflows?

#### Objective 3

The third objective is to describe patient usage patterns to determine adherence and other behaviors in the Medly Program. This objective will answer the following questions:

To what degree do patients adhere to the Medly Program and how do adherence patterns change over time?What factors influence patient adherence?

#### Objective 4

The fourth objective is to evaluate the costs associated with the implementation of the TM program from the perspective of the health care system (ie, public payer), the hospital, and patients.

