##### Data Acquisition

Data collection will occur at baseline, 1 month, 6 months, 12 months, and 24 months, or until the patient exits the program. Data collected in addition to the primary evaluation period (baseline to 6 months) will provide an opportunity for post-hoc analyses aimed at quality improvement, including recommended duration of use. For example, the 1-month time point was included to determine if the bulk of changes to self-care and QoL occur immediately after enrollment. Similarly, longitudinal data will help determine whether patient-level impacts are sustained or change when using the system long term.

Health service utilization, laboratory results, mortality, prediction of survival, and select demographic information will be obtained from the hospital EMR. In addition, health service utilization information will be verified by patient participants through self-reports via a questionnaire.

Baseline and follow-up questionnaires containing the validated survey tools listed in Table 1 will be distributed to patients during regularly scheduled visits. Upon study enrollment, patients will be asked whether they prefer to be mailed the questionnaire or completing it using an online survey tool (SurveyMonkey [38]) in the event that they do not have a clinic visit scheduled for the data collection time point. In these situations, the questionnaires will be sent to the patient according to the preferred format and they will be given 2 weeks to respond, after which a member of the evaluation team will call the patient to remind them to complete the questionnaire.

**Table 1 table1:** Timing of outcome assessments for the impact evaluation.

Domain and measure		Baseline	1 month	6 months	12 months	24 months	Exit

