**Clinical outcomes**							
	Left ventricular ejection fraction	X			X	X	
	Blood work: BNP^b^, creatinine, sodium, potassium, hemoglobin, and uric acid	X		X	X	X	X
	Visual analogue scale for dyspnea	X	X	X	X	X	X
	SHFM^c^	X					

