##### Planned Analyses

The primary analyses will be paired Student *t* tests and Wilcoxon signed rank tests comparing baseline and 6-month values for all patient-level outcomes. For patients enrolled in the Medly Program on hospital discharge, the 30-day readmission rate will be compared with the readmission rate before the launch of the Medly Program, as determined using hospital administrative data. Secondary analyses aimed at determining the longitudinal impact of the Medly Program (ie, using outcome data from the additional time points), and the correlation of independent variables (eg, patient characteristics and adherence rates) with outcomes will be analyzed using general linear mixed model procedures. In addition, descriptive statistics will be produced for all variables collected, which may inform necessary subgroup analyses. All statistical analyses will be performed using the statistical software application SPSS (IBM Corporation, USA) [39].

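### Early change in quality of life, self-care and dyspnea is to be read from all patients together, although some enroll at hospital discharge; it should also be reported by enrollment route

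*Protocol article*

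**What the plan says.** All references are to the protocol article, Objective 1 unless stated otherwise.

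- **Who enrolls.** The objectives anticipate entry at discharge: "For patients who are enrolled into the Medly Program on hospital discharge, the program is expected to reduce 30-day readmission rates". The eligibility criteria (Study Participants, Patients) set no restriction on recent admission, so the sample can mix discharge and ambulatory enrollees. The article does not give the proportions.
- **What the 1-month point is for.** Data Acquisition states that "the 1-month time point was included to determine if the bulk of changes to self-care and QoL occur immediately after enrollment". It says that data outside the baseline-to-6-month period "will provide an opportunity for post-hoc analyses aimed at quality improvement, including recommended duration of use".
- **What is measured when.** Table 1 schedules EQ-5D-5L, MLHFQ, SCHFI and the dyspnea scale at baseline, 1 month and 6 months. Blood work, including BNP, is scheduled at baseline and 6 months but not at 1 month.
- **How it is analyzed.** Planned Analyses specifies paired t tests and Wilcoxon signed rank tests "comparing baseline and 6-month values for all patient-level outcomes". The further time points are assigned to "Secondary analyses aimed at determining the longitudinal impact of the Medly Program (ie, using outcome data from the additional time points"), using general linear mixed models.
- **Where discharge enrollees are separated.** This happens once, for readmission: "For patients enrolled in the Medly Program on hospital discharge, the 30-day readmission rate will be compared with the readmission rate before the launch".
- **Comparator.** Limitations acknowledges that there is none.

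**The concern.** A patient who enrolls at discharge may give a baseline score soon after an acute episode, and scores may then improve over the following weeks with or without telemonitoring. In an uncontrolled before-after design that improvement looks the same as a program effect. It would also tend to fall in the interval that the 1-month questionnaire is meant to examine.

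Two readings are exposed. The first is the pooled baseline-to-6-month change in the questionnaire scores and BNP, which could look like benefit when part of it is recovery. The second is the timing question. An early rise followed by a plateau is what recovery alone would produce, and the article connects the additional time points with a recommended duration of use.

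The article already recognizes discharge enrollees as a distinct group for readmission. It does not state the same separation for the outcomes where their baseline is most open to doubt.

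**Working it through.** **Inputs from the article (Power Consideration).** At least 108 patients, about 20% lost by 6 months, two-sided alpha .05, 80% power, Cohen d = 0.3 for HF hospitalizations.

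**The plan's own figure.** For a paired comparison with d = 0.3, the normal approximation gives ((1.96 + 0.84)/0.3)² ≈ 88 pairs, and 88/0.8 = 110. The exact t calculation gives 90 pairs, and 90 × 1.2 = 108. The stated 108 is therefore reproduced or nearly so, and this point does not depend on it. Expected pairs at 6 months: 108 × 0.8 = 86.4, taken as 86.

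**Assumed inputs, not in the article.**
- Program effect: zero.
- SD of MLHFQ change within each route: 18 points.
- Share enrolled at discharge, s: 10%, 30% or 50%.
- Mean recovery in discharge enrollees, r: 10, 15 or 20 points. Ambulatory enrollees: no mean change.

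**Formulas.**
- Pooled mean change = s × r.
- Pooled SD = √(18² + s(1 − s)r²).
- Apparent d = mean/SD.
- Rejection probability from the noncentral t with 85 degrees of freedom and noncentrality d√86, two-sided .05.

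**Worked case.** With s = 0.30 and r = 15, the mean is 0.30 × 15 = 4.5 and the SD is √(324 + 0.21 × 225) = √371.25 = 19.27. So d = 4.5/19.27 = 0.23, and the test rejects in 57% of studies.

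| Discharge share | Recovery (points) | Pooled mean change | Apparent d | Rejects zero change |
|---|---|---|---|---|
| 10% | 10 | 1.0 | 0.05 | 8% |
| 10% | 15 | 1.5 | 0.08 | 11% |
| 10% | 20 | 2.0 | 0.11 | 16% |
| 30% | 10 | 3.0 | 0.16 | 32% |
| 30% | 15 | 4.5 | 0.23 | 57% |
| 30% | 20 | 6.0 | 0.30 | 78% |
| 50% | 10 | 5.0 | 0.27 | 69% |
| 50% | 15 | 7.5 | 0.38 | 94% |
| 50% | 20 | 10.0 | 0.49 | 99% |

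A second set of assumptions on a standardized scale (change SD of 1 within route, 86 pairs) gives the same picture. A 10% share with recovery of 0.3 SD gives apparent d = 0.03 and 6% rejection. A 50% share with recovery of 0.8 SD gives d = 0.37 and 93%.

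**What the table does and does not measure.** It shows how often a test of zero change would reject because of recovery alone. It does not measure the timing error directly. For timing, let e₁ and e₆ be the true program effects at 1 and 6 months, and suppose recovery is complete by 1 month. The fraction of the 6-month change already present at 1 month is then (s·r + e₁)/(s·r + e₆). With no program effect the fraction is 1. With a slowly building effect (e₁ < e₆) it is pulled toward 1. The direction follows from the assumption, but the article does not allow the amount to be computed.

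**The case against.** The case on the other side is substantial.

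- **The clinical premises are not in the article.** It does not say that discharge enrollees recover in the first month, that they complete the baseline questionnaire near the end of the episode, or that ambulatory enrollees are stable at baseline. Data Acquisition has questionnaires handed out at scheduled visits. This stands: the mechanism is plausible but assumed.
- **Pooling is partly read from silence.** The mixed-model description covers "the correlation of independent variables (eg, patient characteristics and adherence rates) with outcomes will be analyzed using general linear mixed model procedures". That list is open, Planned Analyses mentions possible subgroup analyses, and covariates are often named in a fuller document. This stands in part. The paired tests are nevertheless described for all outcomes, and the only stated split by route is for readmission.
- **The stakes are limited.** Use of the additional time points is labelled post hoc and for quality improvement. Duration of participation is left to patient and cardiologist. This stands.
- **The limitation is disclosed.** Limitations admits heterogeneity and the missing comparator, but treats heterogeneity as a matter of generalizability and does not mention recovery after discharge. Describing context and participants does not separate the two trajectories.

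A reader might go further and infer that the plan will report recovery as a fast program effect, or recommend too short a duration. The documents do not support that: the share, the recovery and the baseline timing are all unknown, and long-term data are also to be used to judge whether effects last. Nor does it follow that speed and duration should be judged from ambulatory enrollees alone, or that discharge enrollees should contribute only their 1-to-6-month change. Ambulatory stability is unverified, and dropping the first month would discard any genuine early effect in discharge enrollees.

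**Conclusion.** The concern holds in a limited form. With both routes analyzed together and no comparator, the plan as described cannot separate recovery after an admission from an early program effect in discharge enrollees. It asks the 1-month questionnaire a question that depends on that separation.

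The size could be anything from negligible to as large as the d = 0.3 used for the sample size, or larger at a 50% share. The 8% to 99% range rests entirely on the assumed share, recovery and SD. It uses the pair count expected at 6 months and concerns a test of zero change.

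The sentence on the 1-month point names self-care and quality of life; dyspnea enters through Table 1. BNP is involved only at 6 months. This is an inexpensive improvement to secondary and exploratory analyses. It does not touch the primary comparison of HF hospitalizations.

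**What to change.** In Planned Analyses for Objective 1, add that:

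1. Changes at 1 and 6 months in EQ-5D-5L, MLHFQ, SCHFI and dyspnea, and the 6-month change in BNP, are reported by enrollment route (discharge or ambulatory) as well as overall.
2. The mixed model includes route and a route-by-time term.
3. Early change in discharge enrollees is not by itself interpreted as a program effect, and is not used alone to support a recommended duration of use.

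The cost is wording only. Enrollment route already has to be identified for the readmission comparison, and no new assessment is needed. The downside is wider intervals within each route, particularly if few patients enroll at discharge.

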**Health service utilization**							
	30-day readmission		X^a^				
	Number of hospitalizations	X		X	X	X	X
	Number of days in hospital	X		X	X	X	X
	Number of emergency department visits	X		X	X	X	X
	Number of heart failure-related outpatient visits	X		X	X	X	X
	Number of visits to family doctors	X		X	X	X	X
	Changes to medication	X		X	X	X	X
**Clinical outcomes**							
	Left ventricular ejection fraction	X			X	X	
	Blood work: BNP^b^, creatinine, sodium, potassium, hemoglobin, and uric acid	X		X	X	X	X
	Visual analogue scale for dyspnea	X	X	X	X	X	X
	SHFM^c^	X					
**Self-care**							
	SCHFI^d^ [37]	X	X	X	X	X	X
	EQ-5D-5L^e^ [34,35]	X	X	X	X	X	X
	MLHFQ^f^ [36]	X	X	X	X	X	X

^a^X: data is collected at this time point.

^b^BNP: brain natriuretic peptide.

^c^SHFM: Seattle Heart Failure Model.

^d^SCHFI: Self-Care of Heart Failure Index.

^e^EQ-5D-5L^:^ EuroQol five-dimensional.

^f^MLHFQ: Minnesota Living with Heart Failure Questionnaire.

##### Planned Analyses

The primary analyses will be paired Student *t* tests and Wilcoxon signed rank tests comparing baseline and 6-month values for all patient-level outcomes. For patients enrolled in the Medly Program on hospital discharge, the 30-day readmission rate will be compared with the readmission rate before the launch of the Medly Program, as determined using hospital administrative data. Secondary analyses aimed at determining the longitudinal impact of the Medly Program (ie, using outcome data from the additional time points), and the correlation of independent variables (eg, patient characteristics and adherence rates) with outcomes will be analyzed using general linear mixed model procedures. In addition, descriptive statistics will be produced for all variables collected, which may inform necessary subgroup analyses. All statistical analyses will be performed using the statistical software application SPSS (IBM Corporation, USA) [39].

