##### Power Consideration

We will aim to recruit at least 108 patients into the Medly Program at the HF clinic before analyses of patient-level outcomes are undertaken. This number is based on being able to detect a small effect size (Cohen *d*=0.3) in the number of hospitalizations because of HF within the first 6 months of enrollment with 80% power and an alpha of .05 (two-sided) [40]. This number considers that approximately 20% of patients will be “lost to follow-up,” which includes patient mortality and those who withdraw from the program before the 6-month time point. We anticipate recruiting this number in the first 18 months of the program.

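### The primary paired tests for the questionnaire scores use only patients with a 6-month value, so health-related loss can bias the mean change in either direction; the planned mixed model should give the main estimate.

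*Protocol article*

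**What the plan says.** Under Objective 1, Planned Analyses, the primary analyses are paired Student t "tests and Wilcoxon signed rank tests comparing baseline and 6-month values for all patient-level outcomes". General linear mixed models that use the other time points appear in the same section, but only as secondary analyses of longitudinal impact and of correlates of outcome.

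Under Data Acquisition, "Data collection will occur at baseline, 1 month, 6 months, 12 months, and 24 months, or until the patient exits the program". Table 1 schedules the dyspnea scale, SCHFI, EQ-5D-5L and MLHFQ at every one of these times and also at exit. The protocol explains that "the 1-month time point was included to determine if the bulk of changes to self-care and QoL occur immediately after enrollment".

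Under Power Consideration, about 20% of patients are expected to be lost, "which includes patient mortality and those who withdraw from the program before the 6-month time point". Limitations acknowledges that there is no distinct comparator group.

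**The concern.** A paired test needs both members of the pair. A patient who answers at baseline and 1 month and is then lost contributes nothing to the primary comparison. Death and the decision to leave the program are plausibly related to health, so the remaining pairs may not represent everyone who enrolled. In a randomized comparison similar selection in both arms could partly cancel. Here the mean change among those who remain is itself the reported effect.

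At stake is whether a modest 6-month change in quality of life, self-care or dyspnea reflects the program or reflects who was left to answer. The ranking of the two analyses is stated in the text, so this is more than a detail that an article leaves to a fuller plan.

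**Working it through.** **The plan's own figure.** Power Consideration aims to "detect a small effect size (Cohen *d*=0.3") "with 80% power and an alpha of .05 (two-sided"). A paired t test then needs 89.15 pairs, taken as 90, and 90 × 1.2 = 108, which is the stated number. Of 108 patients, 108 × 0.8 = 86.4 are expected to provide pairs. Power with 86 pairs is 78.5%, so the size of the study is not the issue.

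**Assumed inputs (not in the protocol).** Score SD 23 points, higher = worse. Correlations are 0.65 (baseline with 1 month), 0.55 (baseline with 6 months) and 0.70 (1 month with 6 months). There is no true change. Loss by 6 months is logistic in a standardized driver z, with odds ratio 1.6 to 4.5 per SD and 20% lost on average. Every patient is taken to have a 1-month score.

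**Formula.** Bias of the mean paired change = SD × slope × h. Here slope is the regression of the standardized 6-month change on z, and h is the mean of z among patients kept. Numerical integration gives h = −0.091 (odds ratio 1.6) to −0.227 (odds ratio 4.5).

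Slopes:
- 1-month worsening: (0.70 − 0.55 − 0.65 + 1)/√(2 × 0.35) = 0.50/0.837 = 0.598
- baseline severity: 0.55 − 1 = −0.45
- 1-month level: 0.70 − 0.65 = 0.05

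Standard error = 23 × √(2 × 0.45)/√86.4 = 21.82/9.30 = 2.35 points. Two-sided rejection = Φ(−1.96 + |bias|/SE) + Φ(−1.96 − |bias|/SE).

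| Loss follows | Paired-test bias (negative = false improvement) | Rejection (nominal 5%) |
|---|---|---|
| 1-month worsening | 23 × 0.598 × h = −1.25 to −3.12 | 8.3% to 26.4% |
| baseline severity | 23 × (−0.45) × h = +0.94 to +2.35 | 6.9% to 17.0% |
| 1-month level | 23 × 0.05 × h = −0.10 to −0.26 | about 5% |

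Simulation (4,000 replicates per case) agrees to within about 0.1 point. A second set of assumed correlations (0.6/0.5/0.6 and 0.7/0.6/0.7) gave the same pattern of signs. When loss followed 1-month worsening, false significant improvement occurred in 10% to 16% of runs, against 2.5% nominal in that direction.

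A larger sample does not help. With the 166 patients reported under Results and an odds ratio of 2.5 per SD of 1-month worsening, rejection rises from about 16% to 22%.

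**The alternative.** This is the likelihood estimate of the 6-month minus baseline mean from baseline, 1-month and 6-month scores.
- In all three cases above its bias was within about 0.1 point.
- Under purely random loss of 20% its variance was about 10% lower than that of the paired mean. Under the strongest loss on 1-month worsening the two variances were about equal.
- If loss follows the unobserved 6-month change, the paired bias is −2.0 to −5.0 points and the model bias −1.2 to −3.0.
- If loss follows the 6-month level, the paired bias is −0.9 to −2.4 points and the model bias −1.0 to −2.9.
- If loss follows a stable latent severity (equal correlations of 0.6), the paired test is essentially unbiased and the model gives −0.4 to −1.2 points.

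**The case against.** **Direction.** A reader might infer that the paired tests will manufacture a benefit. The protocol does not support that. Deaths may follow baseline severity, which biases against improvement. Participation length is set individually by patient and cardiologist (Patients), and Table 2 counts physician-initiated dropouts, so improved patients may also leave. That would reverse the sign of the first row of the table. Nothing in the protocol says that exit follows lack of early improvement. This objection stands, and the point is therefore possible bias of unknown sign.

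**Assumptions.** A reader might infer that the mixed model is safer under every mechanism. It is not. The paired test needs loss to be unrelated to the change, while the model needs loss to be explained by observed scores. Neither condition contains the other, and the last two cases in the working show the model doing slightly worse.

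**Data.** It is tempting to say that most lost patients will have a 1-month score. The protocol gives neither the timing of loss nor a 1-month response rate. It does schedule exit questionnaires, which may give a score later than 1 month for those who withdraw, but it does not say how these enter the 6-month comparison.

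**Already planned, or left to a fuller document.** The mixed model is in the plan, and missing-data rules may be in a document not shown. No fault is found with that silence. What remains is that the named primary test cannot use a patient without a 6-month value unless one is imputed, while a model that can is ranked second.

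**Importance.** These are secondary outcomes, and the lack of a comparator is disclosed. Both are true and limit the weight of the point.

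**Conclusion.** The concern holds in a limited form. For the four questionnaire scores, the stated primary test rests on patients with both values when about 20% loss related to death and withdrawal is expected and no comparator exists. Under the stated assumptions the distortion is about 1 to 3 points of false improvement (1.25/23 = 0.05 to 3.12/23 = 0.14 SD; 8 to 26% rejection), about 1 to 2 points against improvement, or almost nothing, depending on what drives loss. The SD, the correlations and the strength of the loss mechanism are all assumed.

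The mixed model is preferable because it was close to unbiased whenever loss depended on baseline or 1-month scores, whatever the sign of the paired-test bias. It was also clearly less biased when loss depended on the 6-month change. It is not a cure if loss depends on unobserved 6-month scores or stable unmeasured severity. A reader might extend the point to the primary outcome, the count of heart failure hospitalizations. This check concerns only the questionnaire scores and gives no support for that.

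**What to change.** In Objective 1, Planned Analyses, state for the MLHFQ, EQ-5D-5L, SCHFI and dyspnea scale:

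- The main estimate is the 6-month minus baseline contrast from the linear mixed model. It includes all patients with a baseline value and their baseline, 1-month and 6-month scores, with visit as a category and unstructured covariance.
- The paired t and Wilcoxon tests are reported beside it as a sensitivity analysis.
- Deaths are reported separately, with a statement that the model does not define quality of life after death.
- Exit scores are used in a sensitivity analysis for patients who withdraw.
- The missing-at-random assumption is stated, with a note that it differs from the assumption of the paired test and is not strictly weaker.

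The cost is a change of wording and a little more reporting. No new visits, data or patients are needed, and the model is already planned. The downside is reliance on observed scores to explain loss; where they do not, bias remains and can be slightly larger than with the paired test. For that reason both results should be shown.

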#### Patients

Patients can be enrolled into the Medly Program provided they (1) are 18 years or older, (2) have been diagnosed with HF and are followed by a cardiologist at the HF clinic, (3) can speak and read English (or have an informal caregiver who does) to adequately understand the text prompts in the Medly app, and (4) are able to comply with using Medly (eg, able to stand on the weight scale, able to answer symptom questions). As the Medly program is being implemented as part of the standard of care, there is no explicit exclusion criteria for participating in the program and its evaluation. The duration of program participation will be decided by patients and their treating cardiologist on an individual basis.

Upon enrollment into the Medly Program, patients will be presented with the option of answering questionnaires and participating in interviews related to the program evaluation. Patients will be asked to sign a written consent form before participating in the evaluation.

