###### Health Service Utilization

The number of hospitalizations (all-cause), 30-day readmission rate, days in hospital (HF and all-cause), number of ED visits (HF and all-cause), visits to family doctor (HF and all-cause), number of HF–related outpatient visits, and changes to medication will be recorded.

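### The 30-day readmission contrast sets selected Medly enrollees against a pre-launch rate with no stated restriction or adjustment, so it mixes program effect with enrolment selection and calendar time

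*Protocol article*

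**What the plan says.** All references are to the protocol article.

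- **The comparison.** Planned Analyses under Objective 1 says, for patients enrolled on discharge, that "the 30-day readmission rate will be compared with the readmission rate before the launch of the Medly Program, as determined using hospital administrative data". It names no eligibility restriction, calendar window, matching or adjustment for the pre-launch group. The mixed models in the same paragraph are assigned to the longitudinal data and to correlates of outcome.
- **The intended inference.** Under Objective 1 in Evaluation Objectives and Research Questions, for these patients "the program is expected to reduce 30-day readmission rates".
- **Who the enrollees are.** The Patients section requires that they "have been diagnosed with HF and are followed by a cardiologist at the HF clinic", that they or a caregiver can manage the English prompts, and that they "are able to comply with using Medly". In addition, "Patients will be asked to sign a written consent form before participating in the evaluation".
- **How enrollees' utilization is collected.** The Health Service Utilization section lists 30-day readmission as a utilization outcome. Data Acquisition under Objective 1 says: "Health service utilization, laboratory results, mortality, prediction of survival, and select demographic information will be obtained from the hospital EMR". It adds that "health service utilization information will be verified by patient participants through self-reports via a questionnaire".
- **Timing.** Table 1 marks 30-day readmission at 1 month only. It has no baseline entry.

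**The concern.** Most outcomes in this evaluation are compared within patient, baseline against 6 months, so fixed patient characteristics cancel. Thirty-day readmission has no baseline value and cannot be handled that way. It rests wholly on a contrast between two different groups of people in two different periods.

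The program group has passed several filters: follow-up at the clinic, language, ability to use the equipment, the decision to enrol, and consent to the evaluation. As the comparison is written, the pre-launch group need have passed none of them. Any other change in discharge practice or case mix between the periods also enters the difference.

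A lower rate among enrollees could then be read as the reduction the article expects, and a higher or equal rate as a failure of the program. The contrast as described supports neither reading.

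**Working it through.** **1. Figures in the article.** It gives no readmission rate, no number of patients enrolled on discharge and no target difference for this outcome, so there is no stated figure to reproduce. The sample size of 108 belongs to the primary outcome and has no bearing here.

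**2. The two groups side by side.**

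| Feature | Enrolled on discharge | Pre-launch |
|---|---|---|
| Period | after launch in August 2016 | before launch |
| Followed at the HF clinic | required | not stated |
| Language and ability criteria | required | not stated |
| Chose to enrol and consented | yes | not possible |
| Source | hospital EMR, with self-report as verification | hospital administrative data |
| Adjustment | none stated | none stated |

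**3. What the difference estimates when the program does nothing.** Let p be the true pre-launch 30-day rate, s the risk in enrollees relative to the pre-launch group from selection, and c_M and c_H the shares of readmissions captured in the Medly and historical groups. With no program effect:

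observed difference = p·s·c_M − p·c_H

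A calendar-time change in risk multiplies p in the first term exactly as s does, so a given relative change does the same damage.

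**4. Assumed inputs (none from the article).** p = 15% to 25%; s = 0.6 to 1.25; c_H = 80% to 100%; c_M = 95% to 100%.

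*Selection alone (c_M = c_H = 1), difference = p(s − 1):*

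| s | p = 15% | p = 25% |
|---|---|---|
| 0.6 | 0.15 × (−0.4) = −6.0 points | 0.25 × (−0.4) = −10.0 points |
| 0.8 | 0.15 × (−0.2) = −3.0 points | 0.25 × (−0.2) = −5.0 points |
| 1.25 | 0.15 × 0.25 = +3.75 points | 0.25 × 0.25 = +6.25 points |

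*Ascertainment alone (s = 1), which applies only if self-report adds events for enrollees, difference = p(c_M − c_H):*

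| c_M, c_H | p = 15% | p = 25% |
|---|---|---|
| 95%, 80% | 0.15 × 0.15 = +2.25 points | 0.25 × 0.15 = +3.75 points |
| 100%, 80% | 0.15 × 0.20 = +3.0 points | 0.25 × 0.20 = +5.0 points |

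*Both together:* with s = 0.8, c_M = 100% and c_H = 80%, the difference is p(0.8 − 0.8) = 0 at every p.

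**5. Reading.** With no program effect, the difference can be negative, positive or zero. By the same algebra, a real effect could be hidden.

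**The case against.** **Silence is not a decision.** The comparison gets one sentence in a condensed article. A fuller plan could restrict the historical cohort or adjust. This stands in part: the fair statement is that no restriction or adjustment is stated, not that the investigators have ruled one out. But the article does fix which two groups are compared, and followed as written, that contrast is confounded.

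**A reader might infer a firm difference in data source,** EMR plus self-report against administrative data alone. The article does not support that. Data Acquisition under Objective 4 gives EMR data as an example of administrative data. The phrase about administrative data in Planned Analyses can be read as covering both rates. Self-report is described only as verification, and nothing says that readmissions known only from patients enter the count. Ascertainment is therefore a conditional concern.

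**A reader might infer that enrollees are fitter and that the bias favours the program.** The article does not settle the direction. The Patients section says there are no explicit exclusion criteria, and Limitations expects a heterogeneous group. Clinicians may enrol the patients who worry them most, and the sign then reverses.

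**The limitation is already admitted.** Limitations concedes the lack of a distinct comparator group and offers a detailed description of context and participants. It does not mention this historical contrast, and description does not remove confounding from a difference in rates.

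**Scope.** The outcome is secondary and concerns only patients enrolled on discharge. That stands and limits the weight of the point.

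**Conclusion.** The point holds in limited form. The planned contrast mixes program effect with enrolment selection, in an unknown direction, and with calendar time. It mixes in ascertainment as well only if self-reported readmissions count for enrollees and not for the pre-launch group. It cannot by itself show that the program reduced readmission.

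The size cannot be taken from the article. On the assumed inputs, selection alone produces differences from −10 to +6.25 points and unequal capture +2.25 to +5.0 points, and the two can cancel. These figures show what is possible; they do not estimate the bias. A reader might go further and say that the bias exceeds any plausible program effect. The article gives no readmission effect to set against it, so that is unsupported.

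The primary outcome, HF hospitalizations before and after enrolment in the same patients, is not affected by this point.

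**What to change.** 1. **One source, one definition.** Derive the rate in both periods from the same hospital administrative data, with a single definition of index admission, window and qualifying cause. Use self-reported readmissions only in a sensitivity analysis.
2. **Restrict the pre-launch cohort** to HF-clinic patients discharged after an HF admission in matching calendar months before August 2016.
3. **Adjust** for age, sex and admissions in the previous 6 months. Add laboratory values only if they are available for the historical cohort and the number of events allows.
4. **Add a supplementary before/after comparison** of all HF-clinic HF discharges, enrolled or not. It removes enrolment selection, but it dilutes the effect and stays open to calendar-time change.
5. **Report the enrollee-versus-historical contrast as descriptive,** not as evidence that the program reduced readmission.

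The cost is a more specific administrative data request, one regression model and a few sentences in the plan. Historical laboratory values, if wanted, would need separate extraction. No new patient data are required.
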